##### Postpartum Clinical Assessments

The clinical care component of the intervention follows the recommended clinical assessments by the GHS and the WHO and includes assessment of vital signs, fundal assessment, vaginal bleeding or discharge assessment, incision assessment, and a breast examination. After the 6-week postpartum time point, only vital signs are measured at each session. In sub-Saharan Africa, over 60% of maternal deaths occur within the vulnerable first year after birth [2]. Since maternal deaths extend far beyond the traditional 6-week time frame, it is important that quality clinical care extend to 1 after birth. Focused-PPC provides regular contact with and monitoring by a midwife for up to a year following birth.

##### Postpartum Education

The content of Focused-PPC education will focus on the unique needs of postpartum women based on the time frame after delivery. Educational resources will be developed by the research team and an expert panel to apply to different time points throughout the postpartum period and to address the complex needs of postpartum mothers while conforming to the regulations and practices of the GHS. Educational content will then be converted into audiovisual resources, which will be used by midwives to present information during Focused-PPC sessions. Education content will cover the following topics: what to expect for normal postdelivery recovery, self-care, potential postpartum complications and danger signs, risk factors, food and nutrition, breastfeeding, mental health, social support, family planning, menstrual cycles, and interconception care.

##### Postpartum Peer Support

Women in Focused-PPC groups will engage in peer support by discussing issues relevant to them. Group prenatal care models have been shown to improve both pregnancy outcomes and maternal satisfaction with care [25-27]. In the postpartum period, group treatment and peer support programs have been shown to improve postpartum depression and prevent postpartum depression [28-31].

#### Intervention Fidelity

The Focused-PPC intervention will be maintained and monitored through fidelity checklists that are specific to each time point at which a session is held. These checklists will be completed by project assistants and midwives at every session. Additionally, video recordings will be recorded during Focused-PPC sessions at the initial sessions, midpoint sessions, and final sessions. Project assistants will also file session reports that address participant actions and discussions and other session details.

### Data Collection or Measures

In addition to the baseline survey, all participants will be given surveys at 1-2 weeks, 6 weeks, 3 months, 6 months, and 12 months from baseline. All surveys will be interviewer-administered by the project assistants and completed electronically via tablets using a secure database system. Strict procedures will be followed to protect participants’ confidentiality. We also plan to evaluate the feasibility, acceptability, and satisfaction of Focused-PPC. Focus Group Discussions will be conducted with the midwives who implemented Focused-PPC and with each group of participants enrolled in the Focused-PPC intervention arm after their 12-month sessions.

Independent variables and potential covariates will be measured through demographic and obstetric history questions and the Dagbani Readiness for Hospital Discharge Scale-New Mother Form (RHDS-NM). The RHDS-NM is a 22-item instrument that includes a self-reported rating scale with item scores ranging from 0 to 10 and possible scale scores ranging from 0 to 220 [32]. Higher scores indicate greater readiness for hospital discharge. The RHDS-NM, designed for use within English-speaking populations, was translated into Dagbani and adapted for use in Tamale. The Dagbani version of the RHDS-NM has demonstrated excellent reliability (Cronbach ɑ=.94) and measures postpartum mothers’ perceptions of readiness for discharge through examination of their personal status, knowledge, coping ability, and expected support [33].

The primary outcome is knowledge of postbirth warning signs, measured through questions developed based on an evidence-based assessment of the most common postbirth complications. The secondary outcome is postpartum health behaviors, including specific questions assessing health behaviors tailored to the specific time frame postpartum. Other descriptive outcomes include postpartum health status, which will include measures of postpartum depression, stress, complications experienced, vital signs, and other questions on health status as appropriate to the time frame after delivery. Postpartum depression is measured through the Edinburgh Postnatal Depression Scale (EPDS), a self-report screening tool commonly used in perinatal settings [34,35]. The EPDS consists of 10 items assessing women’s depressive symptoms over the past week. The EPDS has a maximum score of 30, with higher scores indicating higher frequency and increased severity of depressive symptoms. Stress is measured through the Perceived Stress Scale (PSS), a 10-item scale assessing women’s stress levels over the last month [36]. The PSS evaluates a woman’s perceptions of unpredictability, lack of control, and overloading in her life, with a higher score indicating higher levels of perceived stress. The feasibility and acceptability of the intervention will be measured using end-project focus group discussion data obtained from midwives and participants in the intervention arm. Outcomes and time points of data collection can be found in Table 1.

### Analysis Plan

Differences in outcomes between the intervention and control arms will be assessed. We expect that the intervention arm will have higher knowledge of postbirth warning signs than the control arm at every time point measured and that the intervention arm will have a larger increase in knowledge of postbirth warning signs between time points. We expect postpartum health behaviors to be different between the intervention and control arms.

All data will be reviewed for completeness and transferred to STATA (StataCorp) statistical software for analyses [37]. The primary variable of interest is knowledge of postbirth warning signs, measured on 4 occasions. The baseline measurement of knowledge of postbirth warning signs will be used in an initial *t* test to confirm that there is no difference in knowledge between the intervention and control arms before the study to validate the randomization procedure. We will model and test the difference between intervention and control arm knowledge of postbirth warning signs at each time point, and knowledge between time points will be assessed using a repeated measures multivariate ANOVA (MANOVA) with a time and treatment interaction as the primary analysis controlling for baseline demographic variables. For the intervention arm, follow-up secondary analyses will measure the change in postpartum health status, postpartum health behaviors, and clinical assessment data over time using repeated measures MANOVA. Ancillary analyses to be run between the intervention and control arms include a proportion test for the patient’s readiness for hospital discharge. Additionally, an evaluation of feasibility, acceptability, and satisfaction will be summarized for inclusion when discussing the cost or benefit of the intervention.

Using intent-to-treat, participants providing data at baseline and first check-in will be included. Missing data (eg, due to attrition) will be accounted for using multiple imputations via the mice package in R (R Core Team) [38]. Sensitivity to missing data will be assessed by comparing multiple imputations to complete case analyses.

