### Sample Size

To establish an appropriate sample size, a power analysis was conducted using G*Power (Erdfelder, Faul, and Buchner) [22,23]. The experimental design has 4 total health centers. Individuals at every health center will be randomly assigned to an intervention arm, keeping in mind that the intervention arm needs to be in multiples of 8 at a time and that intervention groups are equal in size. Baseline characteristics are not expected to affect the outcome. In G*Power, the power analysis was run with 2 groups (the control arm and the intervention arm), which were then split up into 8-equal sized subgroups (health center A intervention, health center A control, ...., health center D intervention, health center D control). The model included 3 time points for measurements. The correlation among repeated measures that varied for a range of values from 0.05 (representing nearly uncorrelated measurements) to 0.3 (representing moderately correlated measurements) was considered. The desired power was always set to 0.8, and the nominal type I error was set to .05. A range of Cohen (1988) effect sizes was evaluated, from 0.10 (very small) up to 0.25 (a medium effect size). The outcome, the mean knowledge of postbirth warning signs, is a continuous variable. This was accomplished by varying the intervention arm’s mean knowledge level. Based on previous study data, 1.9 was used as the control sample’s mean knowledge score, and 1.4 was used as the SD within groups. For the intervention sample, a range of values for the mean knowledge score was tested, from 2.2 (which equates to a 0.1 effect size) to 2.65 (equating to a 0.25 effect size). The control arm and the intervention arm were assumed to have the same SD.

Under optimal conditions, where the correlation among repeated measures is minimal at 0.05 with a medium effect size of 0.25, a total sample size of 64 (16 individuals split into 1 intervention and 1 control group per clinic) is required [24]. Whereas under the worst assumed conditions (a small effect size of 0.10 and any correlation among repeated measures), a total sample size of 512 (128 individuals per clinic split into 16 intervention and 16 control groups) would be necessary. Assuming we want to detect a Cohen f of 0.15 with any size correlation up to 0.3 among repeated measures and no attrition, the recommended sample size is 192 (with 48 individuals split up into 3 intervention and 3 control groups per clinic).

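### The baseline t test on knowledge cannot validate randomisation, and baseline knowledge is given no covariate role in the primary analysis, which costs precision but causes no bias

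*Protocol article*

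**What the plan says.** All references are to the Methods of the protocol article.

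- **Analysis Plan, baseline test.** "The baseline measurement of knowledge of postbirth warning signs will be used in an initial" t test, and its purpose is "to confirm that there is no difference in knowledge between the intervention and control arms before the study to validate the randomization procedure". No action is attached to either result.
- **Analysis Plan, primary model.** A repeated measures MANOVA "with a time and treatment interaction as the primary analysis controlling for baseline demographic variables". Baseline knowledge is not named as a covariate. Differences between arms at each time point are also to be tested.
- **Number of measurements.** The Analysis Plan says "The primary variable of interest is knowledge of postbirth warning signs, measured on 4 occasions"; Table 1 places these at baseline, 1-2 weeks, 3 months and 6 months. The Sample Size section says "The model included 3 time points for measurements". The text does not say whether baseline is one of the modelled responses.
- **Timing.** Under Randomization, the baseline survey is completed before allocation, so every randomised woman should have a baseline score.

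**The concern.** A significance test between randomised arms at baseline asks whether a difference is larger than chance would produce. If the computer-generated list was followed, chance is the only source, so a significant result is a false alarm. A non-significant result does not show that the arms are equal. The test therefore cannot confirm what the plan wants confirmed.

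The better use of the same measurement is as a covariate, and the plan does not state that use. At stake is the precision of the primary comparison. How much is lost depends on whether baseline enters the MANOVA as a response, which the article leaves open.

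**Working it through.** **Inputs (Sample Size and Randomization sections).** N = 192 allocated 1:1, so n = 96 per arm; SD 1.4; Cohen f = 0.15; m = 3 time points; correlation ρ from 0.05 to 0.3; no attrition. For power and error: "The desired power was always set to 0.8, and the nominal type I error was set to .05". The target difference is 2 × 0.15 × 1.4 = 0.42 points, or δ = 0.3 SD.

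**Further assumptions.** One common correlation among all occasions including baseline (compound symmetry), an effect that is constant after baseline, no clustering by care group, two-sided tests.

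**1. The plan's own figure.** Between-arm repeated measures test: λ = f²Nm/[1 + (m − 1)ρ] = 0.0225 × 192 × 3/1.6 = 8.10. With F(1, 190) the power is 0.81. The smallest N for 80% power is 188, and rounding up to a multiple of 64 (4 centres × 16 women) gives the stated 192. So 192 fits a between-arm comparison over three time points without baseline adjustment.

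**2. The baseline t test.** SE of the difference = 1.4 × √(2/96) = 0.20 points. Chance gaps stay within 1.96 × 0.202 = ±0.40 points in 95% of soundly randomised trials. Noncentrality for a 0.42-point gap = 0.3/√(2/96) = 2.08; with 190 df the power is 0.54. The false-alarm rate is 5%.

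**3. Reading A: baseline is one of four responses.** The arm-by-time interaction then compares changes from baseline. For a constant later effect, λ = (n/2) × (3/4)δ²/(1 − ρ), tested on F(3, 188).
- ρ = 0.05: 48 × 0.0675/0.95 = 3.41, power 0.30.
- ρ = 0.3: 48 × 0.0675/0.70 = 4.63, power 0.40.

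With baseline as a covariate, the variance factor of the follow-up mean is v = (1 + 2ρ)/3 − ρ², and λ = (n/2)δ²/v.
- ρ = 0.05: v = 0.364, λ = 48 × 0.09/0.364 = 11.9.
- ρ = 0.3: v = 0.443, λ = 48 × 0.09/0.443 = 9.7.

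| Test | Power, ρ = 0.05 | Power, ρ = 0.3 |
|---|---|---|
| Arm-by-time, four responses (3 df) | 0.30 | 0.40 |
| Baseline-adjusted arm effect, joint (3 df) | 0.83 | 0.74 |
| Baseline-adjusted three-visit mean (1 df) | 0.93 | 0.87 |

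The first two rows are the like-for-like comparison. The third also gains from using 1 df.

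**4. Reading B: only the three follow-ups are modelled.** The unadjusted variance factor of their mean is (1 + 2ρ)/3.
- ρ = 0.3: 0.533 falls to 0.443 with adjustment (−17%). Power rises from 0.81 to 0.87, or N for 80% power falls from 188 to 156.
- ρ = 0.05: 0.367 against 0.364. Power is 0.93 either way.

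**The case against.** Several points on the other side stand.

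- **The baseline gap does not pass straight into the result.** A reader might set the 0.20-point SE against the 0.42-point target and infer that chance imbalance could distort the result by half the effect. In a follow-up comparison only ρ times the gap carries over: 0.3 × 0.20 = 0.06 points (14% of target) at most in the plan's range, and 0.05 × 0.20 = 0.01 points (2%) at the low end.
- **The gain can be negligible.** At ρ = 0.05 under Reading B there is almost none. Correlations above 0.3 would show larger gains, but the plan does not assume them. Nor do the documents show that baseline knowledge is the strongest predictor available; at ρ of 0.05 to 0.3 it explains 0.25% to 9% of follow-up variance.
- **Baseline may already be used.** Under Reading A the interaction takes account of baseline differences, though inefficiently. It is tempting to say that baseline serves only as a fourth response, but that is one of two readings.
- **No decision hangs on the t test.** The article attaches no rule to it, so it does not change the analysis as written.
- **The two sections do not clearly conflict.** A reader might set "Baseline characteristics are not expected to affect the outcome" in the Sample Size section against "controlling for baseline demographic variables" in the Analysis Plan. The first is naturally read as a simplification for the power calculation, and powering without covariates before adjusting for them is ordinary practice.

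None of this gives the t test a valid purpose, and none supplies a reason to leave a pre-allocation measure of the primary outcome out of the covariates.

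**Conclusion.** The point holds as one about a misused test and lost precision. The stated purpose of the baseline t test is wrong on any reading. The cost of giving baseline knowledge no covariate role depends on the unstated role of baseline. It is large if baseline is a response and the interaction is the primary test (like for like, 0.30 against 0.83 at ρ = 0.05 and 0.40 against 0.74 at ρ = 0.3). It is modest to nil if only follow-ups are modelled (0.06 in power at ρ = 0.3, about zero at 0.05).

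A reader might infer that the treatment estimate is biased or the allocation suspect. The documents support neither, since valid randomisation leaves the comparison unbiased with or without adjustment. The figures rest on compound symmetry, a constant effect after baseline, no attrition and no clustering by care group. An effect that grows over the visits would give the interaction more power than shown.

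**What to change.** 1. Delete the baseline t test and its rationale. Report baseline knowledge by arm descriptively (mean, SD, number).
2. Before outcome analysis, state whether baseline knowledge is a response or a covariate, and prespecify one of these, whatever imbalance is observed:
   - baseline knowledge as a covariate for the three follow-up measures, with the arm effect tested overall and at each visit; or
   - a constrained longitudinal model with all four occasions and a common baseline mean, which keeps the time-by-treatment test.
3. With the first option, do not keep the interaction over the three follow-ups as the primary test. A constant effect produces no such interaction, so its power would be only the 5% error rate.

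**Cost.** This is more than a change of wording: the primary model and contrast must be restated and dated, and the Results section reports that all 192 women are already enrolled and randomised. No new data are needed, because baseline knowledge is collected before allocation.

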## Methods

### Study Design

This is a parallel randomized controlled trial with balanced randomization (1:1) conducted in 4 health centers in Sagnarigu municipality, Tamale, Ghana. An overview of the study design can be found in Textbox 1*.*

Study design.Recruitment of potential participantsEnrollment of eligible participantsInformed consent and baseline surveyRandom assignment into intervention and control groups:Kanvilli: 48 participants (intervention: n=24 [3 groups of 8]; control: n=24)Choggu: 48 participants (intervention: n=24 [3 groups of 8]; control: n=24)Kalpohin: 48 participants (intervention: n=24 [3 groups of 8]; control: n=24)Bagabaga: 48 participants (intervention: n=24 [3 groups of 8]; control: n=24)Focused Postpartum Care (Focused-PPC; intervention arm)Focused-PPC careFocus group discussions at endStandard postnatal care (control arm)Usual careNot applicableInterviewer administered surveys at certain time points (see Table 1) for both arms

**Table 1 table1:** Outcomes and evaluation.

Variables	Measurement	Baseline	1-2 weeks	6 weeks	3 months	6 months	12 months
Independent variables and potential covariates	Demographic questions, Obstetric history questions, Readiness for Hospital Discharge Scale – New Mother Form	✓					
Knowledge of postbirth warning signs	Investigator developed questions based on common postbirth complications	✓	✓		✓	✓	
Postpartum health behaviors	Specific questions assessing health behaviors will be tailored to the time frame post partum. Will include attendance to visits		✓	✓	✓	✓	✓
Postpartum health status	Edinburgh Postnatal Depression Scale, Perceived Stress Scale, Questions on complications experienced and other questions on health status as appropriate to the time frame after delivery, Measures of blood pressure, temperature, pulse, and weight	✓	✓	✓	✓	✓	✓
Feasibility, acceptability, and satisfaction	Focus groups with midwives and each group of participants in Focused-PPC^a^ intervention arm using focus group discussion guide						At exit

^a^Focused-PPC: Focused Postpartum Care.

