### Group Conditions

#### Control Arm

Women in the control arm will receive standard postnatal care currently practiced in their respective health centers. This involves attending visits at the health center within 14 days after birth, at 6 weeks, and monthly thereafter up to 1 year. Currently, the GHS recommends beginning postnatal care immediately after birth, with the mother and baby receiving care within 14 days and at 6 weeks. After 6 weeks, the mother attends monthly child welfare clinic visits with the baby for up to 12 months.

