#### Intervention Arm

##### Overview

Each Focused-PPC group in the intervention arm will consist of 8 postpartum women who will meet at 1-2 weeks, 6 weeks, and monthly thereafter for up to 1 year post partum, following the GHS postnatal care schedule. All Focused-PPC group sessions follow a guide developed by the research team with content derived from evidence-based guidelines, reviewed by experts, and approved by the GHS. These group sessions consist of two components: (1) 15-minute individual clinical assessments and counseling for each mother performed by midwives and (2) a 1-hour-long group education session and peer support led by midwives. Each Focused-PPC session will be led by 2 trained and registered midwives from each health center, who will provide both clinical care and education and support as needed. In addition, each group session will be supported by a project assistant, who will be responsible for collecting research data. Focused-PPC will be implemented in addition to newborn care.

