## Results

In the first 6 months of the project, we will complete start-up activities inclusive of inception meetings with GHS representatives at the district and regional levels, developing training guides and Focused-PPC education content, training project staff, and developing data collection tools. In the next 6 months of the project, we will recruit and enroll participants, begin Focused-PPC intervention sessions, and complete data collection. Focused-PPC intervention sessions and data collection will continue in year 2 of the project. End-line focus group discussions will be conducted with project participants and midwives when groups have completed their final intervention sessions at 12 weeks.

Ethical approval was successfully obtained from the Navrongo Health Research Center, and the appropriate approvals were obtained from the GHS. The Focused-PPC Guide (education and session guide) was successfully developed with input from GHS and evidence-based resources and underwent multiple levels of expert review to produce the final guide. All team members, midwives, and project assistants have been trained in the study protocol. Measures for data collection were successfully translated into Dagbani (the local language), and audiovisual resources for the sessions were developed and translated into Dagbani. Clinical trial registration is completed at ClinicalTrials.gov (NCT05280951).

We have enrolled and conducted baseline surveys for 192 women (sample size met) in the Focused-PPC trial who have been randomized into intervention and control arms. We have established a total of 12 Focused-PPC groups in the intervention arm, 3 groups from each site, all of which have sessions underway. Midwives are successfully conducting Focused-PPC sessions using the study’s established guide and protocol. The Focused-PPC intervention is maintained and monitored through fidelity checklists, which are specific to each time point and completed by project assistants and midwives at every session. Project assistants are also documenting sessions through photos, videos, and session reports, addressing participant actions, discussions, and collaboration.

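### The 12 treatment groups of 8 in the intervention arm appear in neither the sample size nor the primary MANOVA, so standard errors are too small and power is overstated for any positive within-group correlation

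*Protocol article*

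**What the plan says.** Study Design describes individual allocation: "This is a parallel randomized controlled trial with balanced randomization (1:1) conducted in 4 health centers". Under Randomization, allocation follows the baseline survey, and women allocated to the intervention also receive a group allocation. The description of the intervention states: "Each Focused-PPC group in the intervention arm will consist of 8 postpartum women who will meet at 1-2 weeks, 6 weeks". Sessions then continue every month to one year. Each session is led by two midwives and includes "a 1-hour-long group education session and peer support led by midwives". Results confirms the count: "We have established a total of 12 Focused-PPC groups in the intervention arm, 3 groups from each site".

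No such groups are formed among controls: "Women in the control arm will receive standard postnatal care currently practiced in their respective health centers". Anticipated Limitations adds that different midwives look after them.

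Sample Size states that "the power analysis was run with 2 groups (the control arm and the intervention arm", and that these were then divided into eight centre-by-arm cells. The groups of 8 enter only as a divisibility constraint. The one correlation considered is between repeated measures, from 0.05 to 0.3. The resulting total is 192 for Cohen f = 0.15, with no attrition.

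For knowledge of warning signs, the Analysis Plan promises arm comparisons at each time point. It then says that "knowledge between time points will be assessed using a repeated measures multivariate ANOVA (MANOVA) with a time and treatment interaction as the primary analysis", adjusted for baseline demographics. No group term appears.

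**The concern.** This is an individually randomized group-treatment trial, clustered in one arm only. Warning signs are among the topics taught in the shared sessions, so the primary outcome is one on which members of a group can be expected to become alike.

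Repeated measures MANOVA handles correlation within a woman and assumes independence between women. If scores within a group are positively correlated, 96 intervention women carry less information than 96 independent women. The arm comparison then gets too narrow a confidence interval and too small a p-value, and the power stated for 192 is not reached by an analysis that is valid. The Conclusions say that the results will be used to refine and scale up the model, so the precision claimed for them matters.

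**Working it through.** **Inputs from the article.** N = 192, 96 per arm; 12 groups of 8 in one arm; 3 time points in the power model (m = 3); f = 0.15; correlation ρ = 0.05 to 0.3; SD 1.4; alpha 0.05; power 0.80. **Assumed, because none is given:** ICC 0.02, 0.05 and 0.10.

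**1. Reproduce 192.** For a between-arm repeated-measures F test of independent women, λ = f²·N·m/(1 + (m−1)ρ). At ρ = 0.3, N = 192 gives λ = 0.0225 × 192 × 3/1.6 = 8.10 and power 0.808 with df 1, 190. The smallest sufficient N is 188. Rounded up to a multiple of 64 (8 women × 2 arms × 4 centres), that is 192. So no allowance for groups is hidden in the total.

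**2. Variance factor.** Clustering multiplies the variance of the intervention mean by 1 + 7·ICC and leaves the control mean alone. The variance of the arm difference is multiplied by (2 + 7·ICC)/2 = 1 + 3.5·ICC.

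**3. Comparison at one visit.** True alpha = 2[1 − Φ(1.96/√(1 + 3.5·ICC))].

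| ICC | Variance factor | SE too small by a factor of | True alpha |
|---|---|---|---|
| 0.02 | 1.07 | 1.03 | 5.8% |
| 0.05 | 1.175 | 1.08 | 7.1% |
| 0.10 | 1.35 | 1.16 | 9.2% |

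**4. Primary time-by-treatment MANOVA.** This was simulated with 4 occasions, an unclustered baseline, 12 groups of 8 against 96 single controls, and no true effect. Over per-visit ICC 0.02 to 0.10, the rejection rate of the nominal 5% test is about 5.6% to 7.5% if the group effect is constant after baseline. It is about 6.6% to 12% if the group effect varies by visit.

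**5. Power of a valid between-arm test.** f = 0.15 means a difference of 2f = 0.30 SD, or 0.30 × 1.4 = 0.42 points. The variance of a woman's 3-visit mean is v = (1 + 2ρ)/3 in SD² units. The noncentrality is 0.30/√[(v/96)(2 + 7·ICC_mean)]. Satterthwaite df use 11 for the 12 groups and 95 for the controls. A persistent per-visit ICC converts to ICC_mean = ICC/v.

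At ρ = 0.3, v = 0.533:

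| ICC | Per visit: ICC_mean | df | Power | Same ICC set on the mean score: power |
|---|---|---|---|---|
| 0.02 | 0.0375 | 32.9 | 74% | 76% |
| 0.05 | 0.094 | 27.1 | 66% | 72% |
| 0.10 | 0.188 | 22.1 | 56% | 66% |

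At ρ = 0.05, v = 0.367 and power without clustering is 93%. With the ICC on the mean score, power is 90%, 87% and 81% at 0.02, 0.05 and 0.10, and 76% at 0.15. A per-visit ICC of 0.02 converts to 0.02/0.367 = 0.055 (power 86%), and 0.05 converts to 0.136 (power 77%).

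**6. Would a plain group intercept repair the primary test?** No. A random intercept equal at all 4 occasions adds the same amount to each of a woman's scores, so it cancels from every contrast between occasions. It would also place a group effect at baseline, before groups exist. The interaction test would stay essentially uncorrected.

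**The case against.** Three stronger readings are tempting, and the article does not support them.

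- **False positives near 13%.** A reader might compute the error rate of an arm test on the mean of the three follow-up visits, which in simulation is 6.4%, 9.0% and 12.9% at ICC 0.02, 0.05 and 0.10. The Analysis Plan lists no such test. It names visit-by-visit comparisons and the interaction MANOVA, and the rates for those are the relevant ones.
- **The 80% power claim fails outright.** The article covers correlations from 0.05 to 0.3, and the shortfall is worst at 0.3. At 0.05, power stays above 80% up to a mean-score ICC of 0.10.
- **A positive result would only reflect a few strong groups.** At ICC 0.02 to 0.05 that is speculation. The article gives no ICC at all.

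Two further points deserve weight. Allocation is balanced within centre, so any centre-level part of the between-group variance is shared with controls. If half of the assumed ICC were of that kind, the arm-mean test above would run at 5.8%, 6.9% and 8.0%. The power run also names centre-by-arm cells, so it is loose to say that it ignores all structure. Those cells do not, however, represent the three groups inside each one.

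Finally, a fuller analysis plan might add a group term. That does not remove the point, because this article itself fixes the model class for the primary analysis and derives its sample size, both without one.

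**Conclusion.** The point holds. The direction is certain for any positive within-group ICC; the size is not, because the ICC has to be assumed. Over 0.02 to 0.10, inflation of the primary test is modest if group effects are constant after baseline (about 5.6% to 7.5%) and can be material if they vary by visit (about 6.6% to 12%). The planned single-visit comparisons fall between (5.8% to 9.2%).

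Power at 192 drops clearly below the target at ρ = 0.3, the worst correlation that the total is said to cover: from 81% to 74% to 56%, or 76% to 66% if the ICC refers to a woman's mean score. At low ρ and low ICC the target survives. These power figures refer to the between-arm test that reproduces 192 and assume no attrition, as the article does.

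**What to change.** Replace the MANOVA with a partially nested linear mixed model:

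- unstructured covariance between visits of the same woman, and health centre as a fixed effect;
- a random effect for Focused-PPC group in the intervention arm only, at post-baseline visits only, and allowed to vary by visit. Alternatively, take baseline knowledge as a covariate and model only the 3 follow-up visits;
- Kenward-Roger or Satterthwaite degrees of freedom, since there are only 12 groups. Name in advance a simpler group-effect structure in case the full one does not converge.

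Use the same group term for the visit-by-visit comparisons and the secondary outcomes. Carry group into the imputation model. Restate power or the detectable difference at N = 192 over a range of ICCs and over ρ from 0.05 to 0.3, saying whether the ICC refers to one visit or to the mean.

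Enrolment is complete, so power can only be restated. Group membership is assigned at allocation, so no new data are needed. The cost is analysis text and one revised power paragraph; the downside is wider confidence intervals and a less favourable stated power.
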